# Effect of YH0618 soup on chemotherapy-induced toxicity in patients with cancer who have completed chemotherapy: study protocol for a randomized controlled trial

**DOI:** 10.1186/s13063-016-1443-9

**Published:** 2016-07-26

**Keywords:** YH0618, Chemotherapy-induced toxicity, Taxanes, Anthracyclines, Dermatologic toxicity, Fatigue, Study protocol

## Abstract

**Background:**

The incidence of cancer has been staying at a high level worldwide in recent years. With advances in cancer diagnosis and therapy strategy, the survival rate of patients with cancer has been increasing, but the side effects of these treatments, especially chemotherapy, are obvious even when the chemotherapy ceases. YH0618, a prescription, has showed efficacy in reducing chemotherapy-induced toxicity through long clinical practice. However, there is no scientific research exploring the effects of YH0618 in patients with cancer. Therefore, using a randomized controlled trial, this study will explore the efficacy of YH0618 on ameliorating chemotherapy-induced toxicity including dermatologic toxicity, myelosuppression, hepatotoxicity and nephrotoxicity and improving fatigue in cancer patients who have completed chemotherapy.

**Methods/design:**

This is a prospective assessor-blinded, parallel, randomized controlled trial. Patients with cancer at any stage who have completed chemotherapy within two weeks will be randomly divided into group A (YH0618) and group B (wait-list) using a 1:1 allocation ratio. The chemotherapeutic agents include taxanes or anthracyclines. Subjects assigned to group A will receive YH0618 soup 6 days a week for 6 weeks and uncontrolled follow-up for 6 weeks, while group B are required to wait for 6 weeks before receiving YH0618 intervention. The primary outcome of this study is the incidence of protocol-specified grade ≥2 dermatologic toxicities graded by NCI CTCAE Chinese version 4.0 and changes of fingernail color, face skin color and tongue color evaluated by the L*a*b system within 6 weeks. There are some secondary outcomes associated with dermatologic toxicity including fatigue and clinical objective examination.

**Discussion:**

There are few scientific and safe methods in ameliorating chemotherapy-induced toxicity. The proposed study may provide direct and convincing evidence to support YH0618 as an adjuvant treatment for reducing chemotherapy-induced toxicity, which could be introduced into clinical settings.

**Trial registration:**

Chinese Clinical Trial Registry: ChiCTR-IOR-15006486. Registered on 21 May 2015.

**Electronic supplementary material:**

The online version of this article (doi:10.1186/s13063-016-1443-9) contains supplementary material, which is available to authorized users.

## Background

According to the data from the WHO’s World Cancer Report 2014, there are an estimated nearly 25 million cancer cases that will occur over the next two decades worldwide, a rise of 75 % [1]. Because of advances in cancer diagnosis and treatment, the survival rate of patients with cancer has been increasing, but the side effects of these treatments, especially chemotherapy, are obvious [2]. Chemotherapy, as a standard regimen, has been used for treating cancers for 70 years. However, in recent years, there is a controversy as to whether it should continue to be used because it causes major side effects, especially toxicity. However, as there is no better regimen to replace chemotherapy, searching for safe and effective ways to ameliorate chemotherapy-induced toxicity has become an urgent issue in the cancer research area.

Chemotherapy-induced dermatologic toxicity is one of the most obvious toxicities, and it can cause considerable cosmetic concern, pain, infection, and functional impairment, and it further impact patients’ quality of life, although it is rarely life-threatening [3, 4]. Its symptoms mainly include pruritus, bullous dermatitis, dry skin, skin pain, paronychia, skin infection, acneiform rash, alopecia, nail discoloration, and nail loss [5]. Low-grade symptoms, such as nail ridging and nail discoloration, can impact beauty and quality of life. Medium-grade symptoms like painful blisters and intense pruritus may also interfere with treatment, resulting in dose reduction or interrupting treatments. Some symptoms may even continue after treatment ceases. Dermatologic toxicity is a major side effect of more than 30 anticancer agents, such as antimetabolites, hormonal agents, topoisomerase-interacting agents, and taxanes; of these taxanes and anthracyclines are the main chemotherapy drugs causing these symptoms [6, 7]. Taxanes are microtubule-stabilizing agents, including paclitaxel, docetaxel, and cabazitaxel, which can stabilize GDP-bound tubulin in the microtubule, therefore interrupting cell division and causing cell death [8]. Anthracyclines are one of the most effective chemotherapeutic drugs and are used to treat many cancers, like lymphomas, leukemias, breast cancer, uterine cancer, ovarian cancer, and lung cancer. The mechanisms of anthracyclines include four pathways. Anthracyclines directly inhibit the synthesis of DNA and RNA by inserting themselves in between nucleotides, thereby interfering with replication and transcription [9]. They also inhibit topoisomerase II, thereby generating reactive oxygen species that damage DNA and cell membranes, or preventing the relaxing of supercoiled DNA and thus blocking DNA transcription and replication [10]. They can also induct histone eviction from chromatin, deregulating DNA damage response, epigenomes, and transcriptomes [11].

Recently, multiple options for reducing chemotherapy-induced dermatologic toxicity have been investigated, but there are no acknowledged and standard treatments. Lacouture et al. [4] found the incidence of grade 2 skin toxicities during the 6-week skin treatment period was 29 % in the pre-emptive group and 62 % in the reactive group. A prospective study demonstrated that ice packs could reduce the incidence of hand-foot syndrome in patients treated with liposomal doxorubicin [5]. In contrast, no significant differences were determined between hand conditions in terms of time to event, nor in terms of toxicity, in cryotherapy and control groups in a randomized control trial [12]. Oral pyridoxine also failed to prevent capecitabine-associated hand-foot syndrome [13].

Chemotherapy-induced myelosuppression, hepatotoxicity, and nephrotoxicity are also common, and they are significant complications affecting the treatment of cancer patients. Moreover, from the view of Chinese medicine, the liver and kidneys are the main organs responsible for detoxification and purification of the blood. Deficiencies of the liver and kidneys lead directly to fatigue, which is also an obvious symptom of cancer patients who just completing chemotherapy. So we believe that dermatologic toxicity and fatigue are a reflection of hepatotoxicity and nephrotoxicity.

Recent attempts to reduce toxicity by using individual compounds have been unsatisfactory [14], and there is also concern about whether using Chinese herbs will cause hepatotoxicity and nephrotoxicity or interactions with anticancer agents [15]; therefore, medical food is the best choice. YH0618, a prescription, has showed efficacy in reducing chemotherapy-induced toxicity through long clinical practice. YH0618 consists of four medical foods (such as black soybeans) which are recommended by clinicians for patients with cancer, and all components have a history of safe use in other foods. Besides, each of the components possesses a distinct pharmacological profile, including removing free radicals in the body, regulating the immune system, preventing cancer, detoxifying, and enhancing taste, etc. [16–18]. Black soybean, as the monarch drug in the prescription, has been used for detoxification over the millennia in China. Modern research has further explored its active compounds and mechanisms in detoxification. Liao et al. [19] found that a novel polysaccharide of black soybean could improve 5-flurouracil- and irradiation-induced myelosuppression in animal experiments. Anthocyanins, which are the main active compounds in the black soybean seed coat, are water-soluble and possess significant anticancer [20], antioxidation [21], liver-protective [22, 23], and kidney-protective effects [24] in vitro and in vivo experiments. Over long clinical observation, YH0618 soup has been proved to be effective in reducing chemotherapy-induced toxicity by clinical observation, but there is not yet any scientific research exploring the effects of YH0618 soup in patients with cancer. Therefore, this study will be conducted to further verify the benefits of YH0618: the hypothesis is that YH0618 soup would ameliorate chemotherapy-induced toxicity including dermatologic toxicity, hematotoxicity, hepatotoxicity, and nephrotoxicity in cancer patients who have completed chemotherapy. Moreover, since little research has explored the role of medical food intervention in reducing chemotherapy-induced toxicity, and YH0618 is a safe medical food, the project will bring huge benefits to patients with cancer. The YH0618 prescription has the potential to become a standard alternative intervention strategy in providing care to these patients.

## Methods/design

### Study design

This is a randomized controlled trial which aims at determining whether YH0618 would be more effective than the wait-list control conditions in ameliorating chemotherapy-induced dermatologic toxicity, blood system disorders, and hepatic and renal disorders and in improving fatigue in cancer patients who have completed chemotherapy. To achieve this goal, a total of 236 patients with cancer at any stage who have completed chemotherapy within 2 weeks will be recruited for the study. The patients will be randomly divided into group A (YH0618) and group B (wait-list) using a 1:1 allocation ratio, adhering to the Consolidated Standards of Reporting Trials (CONSORT) statement [25] and the Standard Protocol Items: Recommendations for Interventional Trials (SPIRIT) statement [26]. The measures of clinical outcomes mainly include the grading of dermatologic toxicity, skin color, nail color, tongue color, and score of fatigue. Several biomarkers associated with myelosuppression, hepatotoxicity, and nephrotoxicity in the blood will also be measured. The flow chart of the study is shown in Fig. 1, and the trial process is listed in Table 1. The evaluation and data collected will be conducted at the clinics of the School of Chinese Medicine, HKU.

**Fig. 1 Fig1:**
[figure not shown]
Flow chart of the clinical trial

**Table 1 Tab1:** Trial process chart

	Before baseline screening	Baseline	Visit 1 Treatment phase	Visit 2 Treatment phase	Visit 3 Follow-up phase
Process items		0 day	3 weeks	6 weeks	12 weeks
Patients					
Inclusion and exclusion criteria	×				
Informed consent		×			
Demographics		×			
Medical history	×	×			
Randomization and allocation concealment		×			
Primary outcomes					
Grading of dermatologic toxicity		×	×	×	×
Objective skin, nail, and tongue color (L*a*b)		×	×	×	×
Secondary outcomes					
Fatigue measurement score		×	×	×	×
Routine blood test (WBC, HGB, PLT)		×	×	×	×
Liver function (ALT, AST, total protein, Alba)		×	×	×	×
Renal function (Cr and BUN)		×	×	×	×
Adverse events			×	×	×
Patients’ diary records		Every day during the study			

### Ethics

Ethical approval of the study protocol was obtained from the Institutional Review Board of the University of Hong Kong/Hospital Authority Hong Kong West Cluster (HKU/HA HKW IRB, reference no. UW15-023). The trial was registered in the Chinese Clinical Trials Registry: ChiCTR-IOR-15006486. Patients will receive a detailed information sheet and complete written consent forms.

The trial is managed by the School of Chinese Medicine, HKU, and data will be supervised by the Data and Safety Monitoring Board (DSMB). Study documents (digital and hard copies) will be retained in a secure location for 5 years after trial completion.

Under the laws of Hong Kong, patients enjoy or may enjoy rights for the protection of the confidentiality of their personal data, such as those regarding the collection, custody, retention, management, control, use (including analysis or comparison), transfer in or out of Hong Kong, non-disclosure, erasure and/or any way of dealing with or disposing of any of their personal data in or for this study. Clinical trial insurance will be provided to the subjects.

### Subjects

A total of 236 eligible patients will be recruited through advertisements. Inclusion criteria include: (1) patients with cancer of any stage aged between 18–75; (2) completed chemotherapy no more than 2 weeks ago; (3) received chemotherapeutic agents containing taxanes or anthracyclines; and (4) a life expectancy of at least 6 months. Exclusion criteria are: (1) subjects with a medical history of dermatosis; (2) any treatment for detoxification within 3 months; (3) any severe mental disorders or history of psychiatric illness or taking psychotropic drugs; (4) severe lesions of liver or kidney; (5) pregnancy or potential pregnancy; (6) allergies to some specific foods, like black soybean, etc. Eligible patients will be invited to participate in this study after providing their written consent form. All participants will be closely monitored in the study. These patients are given open clinical treatment as an additional safeguard.

### Estimation of sample size

The primary outcome in this study is the proportion of subjects with chemotherapy-induced dermatologic toxicity as measured by National Cancer Institute Common Terminology Criteria for Adverse Events (NCI CTCAE) specific grade ≥2. According to previous research, the incidence of NCI CTCAE specific grade ≥2 after the intervention is about 30 % [12]. Our pilot study showed that about 10 % of subjects would have NCI CTCAE specific grade ≥2 after taking the YH0618 soup; thus, the difference in proportion of subjects with dermatologic toxicity between the soup group and waiting-list control group is 20 %. The difference in proportion between the two groups will be examined by a Z-test. To achieve a type I error alpha = 0.05 and power (1 – beta) = 90 %, the minimal number of subjects needed in each group is 82. We estimated a 30 % attrition rate at the end of follow-up; hence, a sample size of at least 118 in each group (236 in total) is planned for this study.

### Randomization and blinding

The research assistant will give each patient a unique study number immediately after they complete the written consent. A computer random digit (randomization list) will be generated by a statistician not involved in this study. Codes representing the two groups will be printed on one A4 opaque paper, and then be put into a envelope which is blotted out using double sided tape. The tape should be torn by the patients themselves just after completing the baseline testing. Because this trial compares the effects of the YH0618 group and the wait-list group, it is not possible to blind the patients; thus, they know which group they are in. However, the randomization sequence and different groups will be kept hidden from the practitioners, data collectors, and statisticians.

### Intervention and control conditions

Prior to intervention, baseline data will be collected including demographics, chemotherapy-induced dermatologic toxicity, skin color, nail color, tongue color, score of fatigue, and the indexes of myelosuppression, hepatotoxicity, and nephrotoxicity in the blood. After that, participants assigned to group A will receive YH0618 soup 6 days/week for 6 weeks and uncontrolled follow-up for 6 weeks, while group B are required to wait for 6 weeks and then receive YH0618 soup for 6 weeks. There is no contraindication between YH0618 soup and chemotherapy, because all the components are general food which people often eat in their daily lives.

### Outcome evaluation

#### Primary outcome

The primary outcome of this study is the incidence of specific grade ≥2 dermatologic toxicities and changes of nail color, skin color, and tongue color after 6 weeks of intervention which will be graded by NCI CTCAE Chinese version 4.0 and evaluated by the L*a*b system, respectively.

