##### Skin, nail, and tongue color measurement

In order to evaluate the changes of skin, nail, and tongue color objectively, L*a*b will be used. The L*a*b system, determined by the International Commission on Illumination (CIE) in 1976, is a “gold standard” in assessing color. In the CIELAB color space, values L*, a*, and b* form a three-dimensional coordinate system by plotting at right angles to one another [28]. Value L* represents light/dark and extends from 0 (black) to 100 (white). Value a* represents the red/green axis, and value b* represents the yellow/blue axis. Recently, many methods are available to measure skin color, such as visual assessment, rating scales, photography, reflectance spectroscopy, etc. After analyzing the advantages and disadvantages of the methods, we decided to adopt digital images in this study. Digital image analysis has been used for more than 15 years in medical imaging; it does not directly contact the skin and therefore cannot disturb the measurement of skin color (e.g., by blanching the skin). The digital camera and environment like lighting source and position, background, and distance between camera and subject will be fixed. First, we will use a Canon® digital camera to take pictures. In order to reduce interference from the external environment, a calibration color chart (Spyder CHECKR 24) will be adopted. Then, the Color Sampler tools in Adobe PhotoShop Creative Suite 6 (CS6) will be used for digital image color analysis, which can retrieve and record L*a*b* color values. We will record the skin color of the forehead, right and left cheeks, jaw, and dorsum of the right and left hands, the nail color of ten fingernails, and tongue color.

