### Statistical analysis

Statistical analysis will be conducted by a statistician using SPSS version 22.0. Analyses will be performed based on intention-to-treat principles, and any missing data in the follow up visits will be imputed using multiple imputation.

Descriptive statistics will be used to summarize the baseline demographics and clinical characteristics for both groups. Missing values at follow-up visits or drop-outs in the two groups will be assessed to identify any potential bias.

For the primary outcomes, relative risk for the incidence of dermatologic toxicities with grade ≥2, including 95 % CIs obtained via normal approximation to the binomial distribution, will be analyzed for the two groups. The changes in nail color and skin color from baseline to 6 weeks will be compared between the two groups by independent sample *t* tests. Because participants will be randomized into the intervention group or wait-list group, little confounding is expected. However, potential confounding variables will be identified as those that differ among treatment groups at baseline and are significantly associated with outcomes. In case any potential confounders are identified, a logistic regression model and a multiple linear regression model will be used to analyze the binary and continuous outcomes, respectively.

In further analyses using measures at all time points, the relative effectiveness of the interventions, including all primary and secondary outcomes, will be assessed in repeated measures mixed models, using the generalized estimating equation (GEE) modeling method. The repeated measures regression models account for the correlations between individual measurements when repeated over time. The primary test of effect depends upon differing patterns of change (slope) over time; thus, differences in slope will be identified by significant interactions of intervention group with time. If the interaction terms are significant, then further analyses will use contrasts within the models to compare groups at each time point and to compare outcomes across time within each group.

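### The primary outcome is one powered proportion in the sample-size section but four outcomes elsewhere, with no stated rule for alpha or success across them

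*Protocol article*

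**What the plan says.** The protocol article defines the primary outcome in five places, and they do not agree.

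- **Estimation of sample size:** "The primary outcome in this study is the proportion of subjects with chemotherapy-induced dermatologic toxicity", counted at grade ≥2. The trial is sized on this alone: 30% against 10%, alpha 0.05, 90% power, 82 per group. Allowing for 30% attrition by the end of follow-up gives 118 per group, 236 in total.
- **Primary outcome:** "the incidence of specific grade ≥2 dermatologic toxicities and changes of nail color, skin color, and tongue color after 6 weeks of intervention".
- **Abstract, Methods/design:** toxicity incidence together with "changes of fingernail color, face skin color and tongue color evaluated by the L*a*b system within 6 weeks".
- **Table 1:** skin, nail and tongue colour appears under primary outcomes, beside the toxicity grading.
- **Statistical analysis:** primary outcomes, in the plural. The proportion gets a relative risk with a 95% CI. For colour, "The changes in nail color and skin color from baseline to 6 weeks will be compared between the two groups" by independent-sample t tests. Tongue colour is not named there; it enters only through the later GEE models, which cover all primary and secondary outcomes.

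The section on colour measurement lists the forehead, both cheeks, the jaw and the backs of both hands, followed by "the nail color of ten fingernails, and tongue color", each read on three colour coordinates.

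**The concern.** A reader cannot tell from this document what a positive primary result would be. One section commits the whole type I error to a single proportion. Three others add three colour outcomes, with no division of alpha, no testing order, and no statement of whether one outcome or all must succeed.

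Two further mismatches make the colour outcomes themselves uncertain: whether skin includes the hands, and whether tongue colour is compared at week 6 at all.

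At stake is the confirmatory claim. The Discussion looks to this trial for evidence strong enough to bring the soup into clinical use. As written, a trial that showed no difference in toxicity could still report a colour difference as a primary result. If alpha were divided later to prevent that, the power calculation would no longer describe the test that is performed.

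**Working it through.** **1. Which outcome does the sample size serve?** Inputs from Estimation of sample size: p1 = 0.30, p2 = 0.10, alpha 0.05, power 0.90, z-test. The sidedness is not stated; two-sided is tried here. With pooled variance under the null and mean proportion 0.20:

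n = [1.960 × √(2 × 0.20 × 0.80) + 1.282 × √(0.30 × 0.70 + 0.10 × 0.90)]² / 0.20²

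= [1.960 × 0.5657 + 1.282 × 0.5477]² / 0.04 ≈ 81.96, so **82 per group**.

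82 / 0.70 = 117.1, so **118 per group** and 236 in total. Both stated figures reproduce. A one-sided test would give 67. Colour plays no part in N.

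**2. How many primary outcomes?** The plain reading of the Primary outcome section is four: toxicity, nail, skin and tongue. Other counts need assumptions that the document does not make:

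- three regions on three coordinates, plus toxicity: 3 × 3 + 1 = 10;
- only the nail and skin t tests, every site and coordinate separate: (10 + 6) × 3 + 1 = 49;
- the same with tongue: (10 + 6 + 1) × 3 + 1 = 52.

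**3. Chance of at least one false positive.** This assumes no effect on anything, 5% per test, and any one success counting as a positive trial. The 5% is inferred from the sample-size alpha and the 95% CI; no level is given for the colour tests. If independent, the chance is 1 − 0.95^k. The correlations are assumed, equal between all tests, and simulated with 200,000 draws.

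| Tests | Independent | Correlation 0.3 | 0.5 | 0.8 |
|---|---|---|---|---|
| 4 | 18.5% | 17% | 16% | 11% |
| 10 | 40% | 35% | 29% | 17% |
| 52 | 93% | 82% | 63% | 30% |

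**4. Power for toxicity if alpha is split.** Power = Φ{[0.20 × √n − z × 0.5657] / 0.5477}, with z the two-sided critical value. For a Bonferroni split over four, alpha = 0.05 / 4 = 0.0125 and z = 2.498.

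- n = 82: (1.811 − 1.413) / 0.5477 = 0.727, power **77%**.
- n = 118: (2.173 − 1.413) / 0.5477 = 1.387, power **92%**.

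At the full alpha of 0.05, power is 90% with 82 per arm. Restoring 90% with the four-way split needs 112 evaluable per arm, or 112 / 0.70 = 160 randomised per arm.

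**5. If every outcome had to succeed.** Each could be tested at 5% without inflating type I error. Overall power would then be at most that for toxicity alone. How much lower cannot be calculated, because no effect size or standard deviation is given for colour.

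**The case against.** The strongest reply is that an analysis plan, not shown here, may hold the alpha split, the testing order and the rule for combining sites and coordinates, and that an article commonly leaves these to it. That is fair as far as it goes, and the absence of such detail is not the point. But no analysis plan can make the sections of this document agree on what the primary outcome is, whether skin includes the hands, or whether tongue colour belongs in the week-6 comparison.

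A reader might go further and infer that the trial runs 52 primary tests at 5%, so that a positive result is likely by chance alone. The document does not support this. The measurement section says where colour is recorded, not that each site and coordinate is a separate hypothesis. The t tests that are named, with toxicity, could give at most 49. The 93% figure also needs independence, which is implausible for ten nails on one hand pair. The document does not rule separate testing out either, so that range stands only as conditional.

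A reader might also infer that splitting alpha would necessarily cost the 90% power. That is not established for four outcomes. The 30% attrition refers to the end of follow-up, which Table 1 puts at 12 weeks; loss by week 6 is not stated. Evaluable numbers may lie anywhere from 82 to 118 per arm, and at 118 the power is 92%.

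Finally, the Primary outcome section joins its components with the word and. If that meant all must succeed, type I error would not rise. No sentence says so.

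**Conclusion.** The point holds as an inconsistent definition of the primary outcome, and it should be fixed. The sample-size section names and powers one proportion; the Abstract, Table 1 and the Primary outcome section add three colour outcomes that have no part in the sample size.

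On the four-outcome reading, with any one success counting at 5% each, the false-positive rate is roughly two to four times the nominal level. A larger inflation depends on separate testing of regions, sites and coordinates, which is neither stated nor excluded. If all four had to succeed, the difficulty becomes unquantified power for colour. Either way a rule is needed, and this document gives none. These sizes rest on an inferred 5% level for colour and on assumed correlations; the contradiction between the sections rests on neither.

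**What to change.** Name the proportion with grade ≥2 dermatologic toxicity at week 6 as the sole primary outcome, tested at two-sided 0.05, as the sample-size section already implies. Change the Abstract, Table 1, the Primary outcome section and Statistical analysis to match.

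Make colour secondary:

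- one summary value per patient for each region (nails, skin, tongue), on one coordinate named in advance;
- one definition of skin, settling whether the hands are included;
- tongue added to the week-6 comparison;
- a fixed testing order, entered only if the primary test is significant;
- other sites and coordinates reported descriptively.

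This should be done before any outcome is compared by group, with the registration and any analysis plan brought into line. N stays at 236, power for toxicity stays at 90% with 82 evaluable per arm, and no new data are needed. The cost is wording, and that colour gives up its primary label. Keeping colour as a defined co-primary with an explicit alpha split or an all-must-succeed rule would also resolve the ambiguity. It would need its own power calculation and, with a four-way split, 112 evaluable per arm to hold 90% for toxicity.
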